**Fig. 1 Fig1:**
[figure not shown]
Study protocol procedure and flow

**Table 1 Tab1:** Study timeline

Timepoint	T_**1**_	T_**2**_	T_**3**_	T_**4**_	T_**5**_	T_**6**_	T_**7**_	T_**8**_	T_**9**_
Enrollment	X	X							
Eligibility screen - EQ5D	X	X							
Informed consent	X	X							
Allocation		X							
Baseline questionnaires - HADS - MFIS - EQ5D - CAREQOL- MS			X						
3-month follow-up questionnaires - HADS - MFIS - EQ5D - CAREQOL- MS				X					
6-month follow-up questionnaires - HADS - MFIS - EQ5D - CAREQOL- MS - CSQ					X				
12-month follow-up questionnaires - HADS - MFIS - EQ5D - CAREQOL-MS						X			
Quality assurance							X		
Data analysis								X	
Results									X

*****Timepoints in 3-month increments; see Abbreviations for list of validated questionnaires provided at baseline, 3-month, 6-month, and 12-month follow-ups

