### Population (inclusion/exclusion criteria)

All adult PwMS who are thought to potentially benefit from NP involvement in their care will be referred to the NP by community neurologists or family physicians and assessed for eligibility and informed consent. Informal caregivers (defined as a partner or close friend who provides for, and/or supports the PwMS) will also be approached to participate in the study. Informal caregivers for PwMS as defined above will be approached to be involved in the study, after the PwMS they care for enrolls in the study and nominates for the inclusion of their caregiver into the study. Consent will be obtained by the software application the PwMS uses to access the study; this will be followed up by the NP and/or neurologist on the first visit.

Inclusion criteria for the study includes:
≥ 18 years of age,Diagnosed with MS as per the clinical 2010 McDonald criteria [78],Followed by a private-practice general neurologist and/or family physician,Willing to provide informed consent,Have the ability to complete questionnaires on their own or with assistance (either by computer or paper copy),Be able to attend outpatient visits with the NP,English-speaking, andWho are experiencing disability from their MS with an Expanded Disability Status Scale (EDSS) between 3.0 and 8.5 or a Patient Determined Disease Steps (PDSS) ≥ 2 [79, 80].

Exclusion criteria for the study are as follows:
People without a diagnosis of MS as per the clinical 2010 McDonald criteria [78],Younger than 18 years of age,Have an EDSS of less than 3.0 or PDDS less than 2,Have a diagnosis of a central nervous system inflammatory disorder other than MS,Are unable to provide informed consent,Are unable to attend visits with the NP in person, or by telehealth.

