Those PwMS who are followed primarily by a family physician, outside of a neurologist, can be referred by their family physician directly to the NP via the established tertiary MS clinic fax system. These referrals will be screened by the NP and one of the researchers (PS, a MS specialist neurologist). Those who meet the eligibility inclusion criteria will be invited to take part in the study. If the patient consents to the study, they will be randomized to either the intervention or control arm as per this study protocol. If the patient is randomized to the control arm, the family physician will be informed that the referral for the NP would be scheduled for after study conclusion: 6 months after the date of referral. Family physicians will be given the additional opportunity of referring the patient to a community neurologist or a NP outside of the study if they feel that the patient cannot wait 6 months for MS specialized care. If the family physician opts for more urgent patient assessment, these patients will be excluded from being involved in the study.

Caregivers will be approached and invited to participate in the study, if the PwMS indicates a caregiver and contact information through their participant consent process. At the end of the informed consent, the PwMS will be asked whether they have a caregiver (with our definition for this study provided). If the participant answers ‘yes they have a caregiver’, they will be invited to provide the caregivers’ name, email address, and/or physical address. A separate informed consent will then be sent to the caregiver by email or by mail, outlining their involvement in the study and seeking their informed consent. Date of first enrolment was July 28, 2017, and recruitment was completed as of March 29, 2019.

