### Data collection

Participants may withdraw from the study at any time without effect to their care. They will be informed they will not receive any incentive for participation and the risks are not beyond the day-to-day risks. After the participants have provided informed consent, they will be invited to complete the questionnaires. PwMS will be asked to complete the Hospital Anxiety and Depression Scale (HADS) [74], Euro Quality of Life Measurement (EQ5D) [23], Modified Fatigue Impact Scale (MSIF) [81, 82], at specific timepoints (baseline, 3 months, 6 months, and 12 months); their caregivers (where applicable) will be asked to complete the Caregiver Health-Related Quality of Life in MS (CAREQOL-MS) questionnaire at the same timepoints [83]. These questionnaires will take approximately 10 to 15 min to complete at each time point. Participants will be asked to keep a participant diary submitted at the same time points, recording the number of outpatient visits and phone calls to their neurologists, family physicians, registered nurses, pharmacists, physiotherapists, occupational therapists, and other allied health professionals (such as massage therapists, chiropractors, dieticians). Alberta has a linked provincial system where all emergency visits and inpatient admissions are recorded. This database will be searched for any emergency visits and inpatient admissions for the 6-month period that the participants are involved in the study.

Participants’ satisfaction with the level of care provided to them will be measured at 6 months at the conclusion of their NP care using the validated Consultant Satisfaction Questionnaire (CSQ) [73, 84]. The CSQ consists of 18 Likert scale questions, ranging from 1 = strongly disagree to 5 = strongly agree, with the higher score indicating a higher level of patient satisfaction.

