### Randomization, allocation, and blinding

This is an interventional study with parallel groups, done through block randomization (variable block sizes) 1:1, using centralized secure website to (1) intervention group (NP-led care) and (2) control group (usual care—community neurologist/family physician and registered nurse (RN), in a non-inferiority framework). The EPICORE Centre will randomize and allocate consented patients who meet eligibility inclusion and exclusion criteria on a 1:1 ratio using a centralized secure website. Block randomization (using variable block sizes) will be used to ensure there are equal participants in the intervention and control arms and to further conceal allocation. The randomization sequence was generated using R blockrand (https://cran.r-project.org/package = blockrand) and the randomization function of REDCap (REDCap Consortium, Vanderbuilt University, Nashville, TN, USA). Participants will be enrolled into the study by the community neurologist’s office (e.g. registered nurse, NP, or neurologist). Participants will register themselves through filling out an iPad questionnaire in the waiting room of community neurologists’ offices, indicating whether they wish to participate in the study or not. The participants, after providing informed consent, will be randomized by the independent EPICORE Centre’s research team to either the intervention group of NP-led care or the control group of standard care provided by community neurologist and registered nurse. After participants have provided informed consent, the EPICORE Centre’s research team will use a centralized website to randomize the patients to either the intervention or control group and then the NP and/or community neurologist will provide the intervention. Participants will be randomized to either the intervention group of NP-led care or the control group of standard care provided by community neurologist and registered nurse. Due to the nature of the intervention, blinding of the providers or patients will not be possible. However, the statistician will be blinded as to which group represents the intervention and control.

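### Caregivers are nominated before allocation, but their consent and first CAREQOL-MS score can follow it in an open-label trial, so the caregiver comparison is only partly protected by randomisation

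*Protocol article*

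**What the plan says.** All references are to the protocol article.

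- **Nomination.** Recruitment: "At the end of the informed consent, the PwMS will be asked whether they have a caregiver". If there is a caregiver, the patient gives contact details at that point.
- **Approach and consent.** Under Population (inclusion/exclusion criteria), the approach comes "after the PwMS they care for enrolls in the study and nominates for the inclusion of their caregiver into the study". Recruitment adds: "A separate informed consent will then be sent to the caregiver by email or by mail".
- **Randomisation.** Randomization, allocation, and blinding: "The EPICORE Centre will randomize and allocate consented patients who meet eligibility inclusion and exclusion criteria". No caregiver step is listed as a condition.
- **Timing of the first score.** Table 1 (Study timeline) has the row "Baseline questionnaires - HADS - MFIS - EQ5D - CAREQOL- MS" at T3, with allocation at T2.
- **Schedule.** Under Data collection, caregivers "will be asked to complete the Caregiver Health-Related Quality of Life in MS (CAREQOL-MS) questionnaire at the same timepoints" as the patients.
- **Blinding.** Randomization, allocation, and blinding: "blinding of the providers or patients will not be possible". Only the statistician is blinded.
- **Use.** Under Outcomes, CAREQOL-MS is a secondary outcome, compared between arms as change from baseline at 3 and 6 months.

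**The concern.** A randomised patient belongs to the trial whatever happens next. A caregiver contributes data only by agreeing to take part. If that agreement is given after the arm is known, the arm can influence who contributes, and the caregivers compared at 3 and 6 months need not be alike apart from the intervention.

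The baseline score has a related weakness. If it is recorded once the arm is known, relief or disappointment about the allocation can move it, and the outcome is measured as change from it. Adjusting for such a baseline does not fully restore the comparison, because the adjustment variable may itself be affected by allocation. The direction is not predictable. A control caregiver who scores worse at baseline out of disappointment has more room to improve, which works against the intervention. Selective joining could work either way.

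At stake is the caregiver conclusion only. The HADS primary outcome in patients does not depend on which caregivers join.

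**Working it through.** The document gives no caregiver number, uptake or CAREQOL-MS standard deviation, so there is no figure of the plan's own to reproduce. The check is mainly one of sequence.

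**1. Order of events**

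| Step | Where stated | Relative to allocation |
|---|---|---|
| Patient consents and names a caregiver | Recruitment | Before |
| Caregiver consent sent by email or mail | Recruitment; Population | After the patient's consent; no link to allocation stated |
| Eligibility check, then randomisation | Recruitment; Randomization, allocation, and blinding | Triggered by the patient alone |
| First CAREQOL-MS | Table 1 | T3, after allocation at T2 |

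Caregiver consent and patient randomisation both start from the patient's consent, and neither waits for the other. A caregiver who replies quickly may precede allocation; one who replies slowly, particularly by post, may not.

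**2. Can the arm be known by then?** Yes. The Intervention arm and Control arm sections have the NP contact patients in both groups to schedule, with a first appointment 4 to 6 weeks after referral in one group and an appointment after the 6-month period in the other. The patient can tell the caregiver.

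**3. Is there a reason for behaviour to differ by arm?** The abstract's Methods paragraph has the NP provide care to the caregiver as well as the patient at the baseline visit. Questionnaire prompting also differs: the NP asks about completion at visits in the intervention arm, while the coordinating centre makes contact in the control arm.

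**4. Which steps are exposed?** Nomination is not. Caregiver consent and the baseline score are, for those who respond after allocation.

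**5. Does the analysis repair it?** Statistical analysis uses t-tests with last observation carried forward and applies the same methods to secondary outcomes. Neither corrects for who agreed to join.

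**6. Illustration on assumed values only.** Suppose consenting caregivers are of two types whose mean change differs by d standard deviations of change, and the share of one type differs between arms by p. With no treatment effect:

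- spurious difference = d × p;
- standard error = √(2/n), with n caregivers per arm;
- chance of a significant result at two-sided 5% = 1 − Φ(1.96 − dp/SE) + Φ(−1.96 − dp/SE).

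At the mild end, d = 0.5, p = 0.10 and n = 30: the difference is 0.05 SD, SE = √(2/30) = 0.258, and the false-positive rate is 5.4%. At the strong end, d = 1.0, p = 0.20 and n = 80: the difference is 0.20 SD, SE = √(2/80) = 0.158, and the rate is 24.4%. None of these inputs comes from the document. They show only that the effect could run from negligible to material.

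**The case against.** The strongest reply is that caregiver consent after allocation is inferred and nowhere stated. The form is sent following the patient's consent, and enrolment is not allocation: Table 1 gives them separate rows, with enrolment spanning T1 and T2. Data collection ties the questionnaires to consent and does not mention allocation. Table 1 is also not a literal calendar. Its footnote speaks of 3-month steps, yet the 6- and 12-month visits sit in adjacent columns. A condensed article may omit the operational order in which forms are released. Finally, control patients are offered the NP later, which weakens one motive for uptake to differ.

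Much of this stands. It rules out saying that every caregiver consents and scores after allocation. It does not remove the point: the only stated ordering of allocation and first CAREQOL-MS puts the score later, and the randomisation section describes a trigger that leaves the caregiver out. Followed as written, the plan permits both steps to occur with the arm known.

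A reader might go further and infer that the whole caregiver group is chosen after allocation, so that the CAREQOL-MS comparison is not randomised at all. The documents do not support that. Nomination precedes allocation, so the nominated list is a protected denominator, and some caregivers may also have consented and scored before allocation.

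**Conclusion.** The point holds in a limited form. For at least some caregivers, joining and the baseline score may be influenced by knowledge of the arm, so the CAREQOL-MS change comparison at 3 and 6 months is only partly protected by randomisation. This rests on three things: the T2 and T3 ordering in Table 1 being meaningful, the absence of any hold on randomisation for the caregiver, and the lack of blinding.

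The size and direction of any bias cannot be derived from the document; the range in the illustration follows from assumed inputs. The consequence is confined to one secondary outcome, and the point is a minor one for the trial as a whole.

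**What to change.** **In the plan, or for a future trial of this design.** Send the caregiver consent and baseline CAREQOL-MS as soon as the patient names a caregiver. Release the allocation once the caregiver has replied or a short fixed window has closed. The cost is a brief delay for patients who name a caregiver.

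**For the existing data.** Recruitment and Trial status both report recruitment as complete, so allocation can no longer be held. Trial status places final quality assurance and analysis still ahead, so the following can be added:

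1. Take all nominated caregivers as the denominator, by arm.
2. Tabulate consent and return of baseline CAREQOL-MS by arm, and by date relative to allocation where dates are available. The article does not say that caregiver consent dates were stored, and some forms may be on paper.
3. Run a sensitivity analysis restricted to caregivers who consented and gave baseline before allocation. It may leave few caregivers, so it should not replace the main comparison.
4. Describe the CAREQOL-MS result as exposed to possible post-randomisation selection, and limit the conclusions accordingly.

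The cost is one table, one extra analysis and a sentence of interpretation.

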### Data collection

Participants may withdraw from the study at any time without effect to their care. They will be informed they will not receive any incentive for participation and the risks are not beyond the day-to-day risks. After the participants have provided informed consent, they will be invited to complete the questionnaires. PwMS will be asked to complete the Hospital Anxiety and Depression Scale (HADS) [74], Euro Quality of Life Measurement (EQ5D) [23], Modified Fatigue Impact Scale (MSIF) [81, 82], at specific timepoints (baseline, 3 months, 6 months, and 12 months); their caregivers (where applicable) will be asked to complete the Caregiver Health-Related Quality of Life in MS (CAREQOL-MS) questionnaire at the same timepoints [83]. These questionnaires will take approximately 10 to 15 min to complete at each time point. Participants will be asked to keep a participant diary submitted at the same time points, recording the number of outpatient visits and phone calls to their neurologists, family physicians, registered nurses, pharmacists, physiotherapists, occupational therapists, and other allied health professionals (such as massage therapists, chiropractors, dieticians). Alberta has a linked provincial system where all emergency visits and inpatient admissions are recorded. This database will be searched for any emergency visits and inpatient admissions for the 6-month period that the participants are involved in the study.

Participants’ satisfaction with the level of care provided to them will be measured at 6 months at the conclusion of their NP care using the validated Consultant Satisfaction Questionnaire (CSQ) [73, 84]. The CSQ consists of 18 Likert scale questions, ranging from 1 = strongly disagree to 5 = strongly agree, with the higher score indicating a higher level of patient satisfaction.

### Randomization, allocation, and blinding

This is an interventional study with parallel groups, done through block randomization (variable block sizes) 1:1, using centralized secure website to (1) intervention group (NP-led care) and (2) control group (usual care—community neurologist/family physician and registered nurse (RN), in a non-inferiority framework). The EPICORE Centre will randomize and allocate consented patients who meet eligibility inclusion and exclusion criteria on a 1:1 ratio using a centralized secure website. Block randomization (using variable block sizes) will be used to ensure there are equal participants in the intervention and control arms and to further conceal allocation. The randomization sequence was generated using R blockrand (https://cran.r-project.org/package = blockrand) and the randomization function of REDCap (REDCap Consortium, Vanderbuilt University, Nashville, TN, USA). Participants will be enrolled into the study by the community neurologist’s office (e.g. registered nurse, NP, or neurologist). Participants will register themselves through filling out an iPad questionnaire in the waiting room of community neurologists’ offices, indicating whether they wish to participate in the study or not. The participants, after providing informed consent, will be randomized by the independent EPICORE Centre’s research team to either the intervention group of NP-led care or the control group of standard care provided by community neurologist and registered nurse. After participants have provided informed consent, the EPICORE Centre’s research team will use a centralized website to randomize the patients to either the intervention or control group and then the NP and/or community neurologist will provide the intervention. Participants will be randomized to either the intervention group of NP-led care or the control group of standard care provided by community neurologist and registered nurse. Due to the nature of the intervention, blinding of the providers or patients will not be possible. However, the statistician will be blinded as to which group represents the intervention and control.

### Drop-out criteria

Participants may withdraw and drop out of the study at any time, for any reason. They may continue with their regular neurologist, family physician, and the nurse practitioner for clinical reasons, outside of the study setting if they decide to drop out.

Drop-out criteria would include:
Lack of response to research team contact on three occasionsIndication to the research team that they wish to drop out of the study and not continue in the study for any reason.

### Individuals who will perform the interventions

The NP will deliver care to those participants randomized to the NP-led care arm during the 6 months of study duration in addition to participants’ regular healthcare providers, while the participants’ regular community neurologists and family physicians in addition to their registered nurses will deliver care to those participants in the usual care arm. There will be one NP participating in the study. She was hired as a general NP, with no specialized skills in MS. However, before moving into the community neurologist environment, she will be mentored and trained for a 3-month period by the MS clinic NP, who has over 6 years of experience in MS, and MS clinic subspecialist neurologists. All the education resources, treatment approaches, interventions, and referral patterns from the MS clinic will be shared with the NP who will be participating in the study. One of the MS clinic neurologists (primary author of this paper, PS) and the MS clinic NP will be continuing to mentor and support this NP through the study. After training at the MS clinic, the study will start after the NP has worked in the community setting for 1 month. This will allow her to orient herself, to understand community neurologists’ practices and approaches, and amalgamate with what she has learned from the MS clinic. This is being done to ensure that the NP involved in the study is comfortable and supported in her approach to supporting PwMS, and to minimize learning curves or experience effects through the study. An information session for the community neurologists and the NP will be set up prior to initiating the study, outlining the study protocol. There are no specific requirements or training for family physicians or community neurologists to have their patients participate in the study. This will ensure their ‘usual’ practice of how they treat PwMS. The administration of surveys and outcome assessments are being done by EPICORE Centre and sent to participants directly. Therefore, no training needs to be done by the NP, community neurologists, or family physicians in this study.

There are no methods to ensure fidelity of participants to the intervention arm or control arm. The NP is backed up by the community neurologists during the 6 months that she is leading care for participants in the intervention arm. Therefore, she will be writing reports and summaries to the neurologists and family physicians after seeing participants and may ask questions of the community neurologists as to their preferences in treatment approaches (e.g. disease-modifying therapies, treatment of relapses with steroids) in individual situations. This is within the study outline, as the NP is an add-on to the care team for the patients, and primarily leads an intervention of care for the participants, with regular follow-ups at baseline, 3 months, and 6 months, with as-needed appointments or phone calls in between regular follow-up visits.

